## 6. Treatments

Patients meeting the eligibility criteria and signing the informed consent will be randomized. Patients randomized to the interventional arm will receive BMM plus EVT. Artery puncture should be performed within 1 hour of randomization. Patients randomized to the medical arm will receive BMM.

### 6.1 Endovascular Therapy (EVT)

When the patient's condition permits, local anesthesia is the first choice for rapid initiation of puncture and endovascular therapy. If the condition requires, sedation can be used, and intubation can be considered for patients at high risk of airway collapse.

If the patient is expected to have poor intraoperative cooperation even with sedation or is at high risk of using sedation or airway conditions due to the patient's illness, general anesthesia should be used. Return to the Neuro-Intensive Care Unit (NICU) with intubation or not should be determined according to the surgical results.

Systemic heparinization is not recommended for preoperative and intraoperative treatment. Femoral artery is suggested for arterial puncture, and long sheath, guiding catheter or balloon guiding catheter can be used. Stent retriever (Solitaire, EMBOTRAP, Reco, Captor or other first-line stent retriever systems) and/or contact aspiration (Penumbra aspiration system or other first-line aspiration system) are recommended as the first choice for thrombectomy. If successful reperfusion (eTICI 2b50-3) is not achieved after routine thrombectomy, other techniques are allowed for rescue treatment, including replacement of thrombectomy technique, replacement of thrombectomy device, intra-arterial thrombolysis, balloon angioplasty or stent implantation, etc. The need for rescue treatment is defined (including, but not limited to, a decision made by the investigator based on intraoperative conditions) as follows: three times of thrombectomy with the same thrombectomy device (stent or suction catheter) without successful recanalization; Target vessels were successfully recanalized and reoccluded again; Target vessel dissection or stenosis  $\geq 70\%$ , with any degree of forward blood flow disturbance; New lumen/stent thrombosis resulted in a decreased of eTICI score.

All the above operations should be performed using devices approved by the National Medical Products Administration (NMPA) and should be performed in accordance with the approved intended use and operating instructions.

## **6.2 Best Medical Management (BMM)**

All enrolled patients should receive BMM in accordance with the recommendation of “Chinese Stroke Association guidelines for clinical management of cerebrovascular disorders” by Chinese Stroke Association (CSA). This includes IV thrombolysis therapy for patients meeting the guidelines. Patients who plan to undergo or are undergoing IV thrombolysis therapy can decide whether to terminate IV thrombolysis

therapy in advance according to the investigator's judgment after enrollment. Patients who had completed IV thrombolysis prior to randomization are also eligible for inclusion in this study. All patients will be required to record the name, dosage and time of IV thrombolysis medication in detail. Antiplatelet agents are not recommended within 24 hours after IV thrombolysis unless the patient has undergone balloon dilatation or stent implantation, at which time the antithrombotic strategy is determined by the investigator. Based on the time window and infarct core volume for ANGEL-ASPECT, it is anticipated that most patients enrolled in ANGEL-ASPECT will not have received IV thrombolysis prior to randomization. Non-IV thrombolysis patients will be treated with aspirin, unless an indication for early anticoagulation is present.

## **7. Study endpoints**

### **7.1 Primary efficacy endpoint**

90 days ( $\pm 7$  days) modified Ranking Scale (mRS)

### **7.2 Secondary efficacy endpoint**

- (1) 90 days ( $\pm 7$  days) mRS 0-2
- (2) 90 days ( $\pm 7$  days) mRS 0-3
- (3) 36 hours ( $\pm 12$  hours) NIHSS 0-1 or decrease  $\geq 10$  from baseline
- (4) Infarct core volume change from baseline, at 7 days ( $\pm 1$  day) or at discharge assessed with NCCT or at 36 hours ( $\pm 12$  hours) assessed with MRI
- (5) 36 hours ( $\pm 12$  hours) target artery recanalization rate assessed with CTA or MRA

### **7.3 Primary safety endpoint**

Rate of sICH within 48 hours from randomization (Heidelberg Bleeding Classification, Appendix 5)

## **7.4 Secondary safety endpoint**

- (1) All-cause mortality within 90 days ( $\pm 7$  days)
- (2) Any intracranial hemorrhage within 48 hours from randomization (Heidelberg Bleeding Classification)
- (3) Decompressive hemicraniectomy during hospitalization

## **8. Data collection and Study procedure**

Investigator(s) should keep a record, the eligibility Case Report Form (CRF), of subjects who enter pre-study screening. The sub-center number must be indicated. The screening table will be used to analyze and determine whether the enrolled patients in different study sites are representative. Referring to the procedure manual and data collection guidelines, investigators should guarantee the input of CRF is precise, complete and timely, and answer the queries in time. Brain imaging which includes: CT, CTA, CTP, MRI (T1+T2+DWI+FLAIR+ADC+GRE-T2\*/SWI+MRA±PWI) and DSA will be collected as DICOM format. Laboratory results will be collected in photocopies of the reports.

### **8.1 Screening and Inclusion**

- Basic data collection: hospital name, name of patient identification, age, sex, allergy to contrast agent.
- History of present event: time of onset (time of last known well), time of arrival at the hospital, type of onset, IV thrombolysis after onset (initial time, name and dose of the drug).

- Medical history and medication before onset

Medical histories (smoking, drinking, hypertension, diabetes, dyslipidemia, cardiac arrhythmia, valvular heart disease, cardiac insufficiency, coronary atherosclerotic heart disease, peripheral arterial disease, TIA, cerebral infarction, cerebral hemorrhage, intracranial tumors), pre-stroke mRS;

Combination therapy: Antiplatelet drugs (aspirin, clopidogrel, cilostazol, prasugrel, ticagrelor, ticlopidine, etc.), anticoagulants (warfarin, dabigatran, rivaroxaban, apixaban, edoxaban, heparin, argatroban, etc.), statins (atorvastatin, pitavastatin, rosuvastatin, pravastatin, simvastatin, fluvastatin, etc.).

- Physical examination

Height and weight, blood pressure, pulse, neurological evaluation (NIHSS and Glasgow scale), 12-lead electrocardiogram (ECG) .

- Emergency laboratory examinations

Emergency blood routine, emergency renal function, emergency liver function (transaminase), emergency coagulation, random blood glucose, etc.

- Imaging

A head CT is required to rule out hemorrhage and perform ASPECTS evaluation; a CTA or MRA is essential to confirm the occlusion artery; a CTP or MRI is required to calculate the infarct core volume

- All participants or his/her need to sign a written informed consent form
- Included subjects will be randomized

## 8.2 Data to be collected during procedure

- General anesthesia with intubation or conscious sedation with local anesthesia at start of procedure
- Procedure times: groin puncture time, time of each pass finish, time of initial flow restoration, time of successful recanalization and the end of the procedure
- eTICI score: pre-procedure and post-procedure
- Details of procedure: Accessory and adjunctive devices used (guide catheter, guidewire, intermediate catheter, microcatheter), number and type of devices for thrombectomy, number of recanalization attempt deployments, rescue procedures with medications besides thrombectomy
- Medication during the procedure: heparin, tirofiban, alteplase, urokinase.
- Intraprocedural complications: Presence of vasospasm (time of onset, vessels involved, time resolved, treatment required), evidence of clot migration or embolization, dissections, perforations, etc.

## 8.3 Post Treatment (Through Hospital Discharge)

A face-to-face observation will be performed at 36 hours ( $\pm 12$  hours) and 7 days ( $\pm 1$  day)/at discharge which is earlier after randomization.

- Brain imaging performed at 36 ( $\pm 12$ ) hours after randomization: CT/CTA or MRI/MRA.
- A physical exam, as well as clinical and neurological assessments, will be completed at 36 ( $\pm 12$ ) hours and 7 ( $\pm 1$ ) days/at discharge which is earlier after randomization. Data to be collected include: vital signs (blood pressure and heart rate), relevant concomitant medications (including antiplatelet, anticoagulant, and antihypertensive agents), significant findings from clinical assessment and physical exam (i.e. all new, worsening, or improved conditions), all significant neurological findings, NIHSS Score (both), mRS (7 days or discharge only), and adverse event (AE).
- Head CT evaluation is needed at 7 days ( $\pm 1$  day) or at discharge whichever is earlier

- Laboratory examinations will be collected at 24 hours ( $\pm 12$  hours) and 7 days ( $\pm 1$  day) or at discharge whichever is earlier after randomization, including: blood routine, renal function, liver function, coagulation, fasting blood glucose, etc.

#### **8.4 Follow-up Visit at Day 30 ( $\pm 3$ ), Day 90 ( $\pm 7$ ) and 12 Months ( $\pm 14$ days)**

These follow-up evaluations can be performed via telephone if it's not convenient for an in-person visit at the investigational site. All subjects entered into the study will undergo a standard neurological assessment by experienced physicians who are blinded to treatment assignment. Data to be collected include:

- mRS
- Patient-reported functional health status and quality of life using EuroQoL 5-Dimensions 5-Level questionnaire (EQ-5D-5L)
- Relevant concomitant medications
- Significant findings from clinical assessment and physical exam (i.e. all new, worsening, or improved conditions since discharge)

#### **8.5 Unscheduled Follow-up Visit**

If an unscheduled follow-up visit occurs after randomization at the investigational site during the study, the incidence of any new or unresolved AEs will be assessed. If the visit is due to a change in neurological status, NIHSS and mRS will be completed by a certified rater.

## 8.6 Schedule of activities and assessments

| Measurements                        | Baseline       | 36-hour
(±12 hours)
visit | 7±1 day
/at discharge
visit | 30-day (±3
days) visit | 90 days
(±7 days)
visit | 12-month ±14
days visit |
|-------------------------------------|----------------|---------------------------------|-----------------------------------|---------------------------|-------------------------------|----------------------------|
| Informed Consent                    | x              |                                 |                                   |                           |                               |                            |
| Inclusion/Exclusion                 | x              |                                 |                                   |                           |                               |                            |
| Randomization                       | x              |                                 |                                   |                           |                               |                            |
| Demographic characteristics         | x              |                                 |                                   |                           |                               |                            |
| History of present illness          | x              |                                 |                                   |                           |                               |                            |
| Past medical history                | x              |                                 |                                   |                           |                               |                            |
| Relevant Concomitant
Medications | x              | x                               | x                                 | x                         | x                             | x                          |
| mRS                                 | x              |                                 | x                                 | x                         | x                             | x                          |
| NIHSS                               | x              | x                               | x                                 |                           |                               |                            |
| Head CT                             | x              |                                 | x                     |                           |                               |                            |
| CTA±CTP or
MRI*+MRA±PWI          | x  |                                 |                                   |                           |                               |                            |
| CT+CTA or MRI*+SWI+MRA              |                | x                   |                                   |                           |                               |                            |
| Carotid CTA/MRA/ultrasound          |                | x                   |                                   |                           |                               |                            |
| ASPECTS on CT                       | x              |                                 |                                   |                           |                               |                            |
| Ischemic volume on CTP/DWI          | x              | x                   | x                     |                           |                               |                            |
| Laboratory examinations             | x              | x                               | x                                 |                           |                               |                            |
| Electrocardiogram                   | x              |                                 |                                   |                           |                               |                            |
| TOAST                               |                |                                 | x                                 |                           |                               |                            |
| EQ-5D-5L scale                      |                |                                 |                                   | x                         | x                             | x                          |
| AE/SAE                              |                | x                               | x                                 | x                         | x                             | x                          |

 For all enrolled cases, CT+CTA+CTP examination was the first choice before randomization

 All the enrolled cases should be reviewed with multi-mode imaging 24-48 hours after randomization, and the image evaluation method should be the same as before randomization

 All enrolled cases should be examined by head CT at 7 days (±1 day) after randomization or at discharge which is earlier

 It was only applicable to patients in the standard medical treatment group who did not undergo cervical angiography prior to randomization

 Based on head CT or MRI, determined by the core imaging laboratory

\*MRI sequence includes T1+T2+DWI+ADC+FLAIR sequence

ADC: apparent diffusion coefficient; AE: adverse event; ASPECTS: Alberta stroke program early computed tomography score; CT: computed tomography; CTA: computed tomography angiography; CTP: computed tomography perfusion; EQ-5D-5L: EuroQoL 5-Dimensions 5-Level questionnaire; FLAIR: fluid attenuated inversion recovery; MRA: magnetic resonance angiography; MRI: magnetic resonance imaging; mRS: modified Rankin scale; NIHSS: National Institutes of Health Stroke Scale; PWI: perfusion weighted imaging; SAE: serious adverse event; SWI: susceptibility weighting imaging; TOAST: Trial of ORG 10172 in Acute Stroke Treatment.

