### **1.5 ANGEL-ASPECT Trial design**

ANGEL-ASPECT trial is a PROBE study initiated by researchers to explore the effectiveness and safety of EVT in patients with anterior circulation large vessel occlusion with ASPECTS 3-5 or infarction core volume 70-100ml within 24 hours. ANGEL-ASPECT trial allows multiple imaging modalities to screen for LICV patients, but at the same time imposes certain limitations on the range of ASPECTS or infarct core volume. The main purpose was to reduce the risk of EVT while enrolling as many LICV patients as possible. The primary image inclusion criteria of ANGEL-ASPECT was NCCT-ASPECTS 3-5, and the infarct core volume 70 ml-100 ml was used as auxiliary inclusion criteria. Briefly, the inclusion criteria for LICV are: (1) If NCCT-ASPECTS is 3-5 and presentation is within 24 hours of onset, patients are enrolled without limitation of infarct core volume. (2) For NCCT-ASPECTS 0-2 and core infarction volume 70 ml-100 ml, patients are enrolled. (3) If NCCT-ASPECTS is >5 and between 6 to 24 hours from symptom onset, only patients with infarct core volume 70 ml-100 ml are enrolled.

Subgroup analysis will focus on age, LKW to randomization time, NIHSS score, IV thrombolysis, occlusion site, ASPECTS, infarct core volume, and stroke etiology.

ANGEL-ASPECT is the only randomized controlled trial conducted in China for LICV patients so far. The results of this trial will clarify whether EVT is effective and

safe in Chinese LICV patients.

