### **36h (24-48h) infarct volume change (by CT or MRI)**

The change of 36h (24-48h) infarct volume change (by CT or MRI) will be analyzed using student t-test or Wilcoxon rank sum test as appropriate.

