### 8.1 筛选和入组

- 基本信息：中心编号，患者编号，年龄，性别，是否造影剂过敏。
- 现病史：起病（最后正常）时间，到达急诊时间，起病形式，起病后静脉溶栓情况（开始时间，药物名称和剂量）。
- 既往病史和发病前合并用药

既往病史（吸烟、饮酒、高血压、糖尿病、高脂血症、心律失常、心脏瓣膜病、心功能不全、冠心病、外周血管病、短暂性脑缺血发作、脑梗死、脑出血、颅内肿瘤），起病前 mRS;

合并用药：抗血小板药（阿司匹林、氯吡格雷、西洛他唑、替格瑞洛等），抗凝药（华法林、达比加群、利伐沙班等），他汀类（阿托伐他汀、匹伐他汀、辛伐他汀等）。

- 体格检查

身高, 体重, 血压, 脉搏, 神经功能评估 (NIHSS 和 Glasgow 评分), 12 导联心电图。

- 急诊实验室检查

急诊血常规, 肾功能, 肝功能, 凝血项, 随机血糖等。

- 影像检查

需完善头 CT 检查排除出血性疾病, 并依此进行 ASPECT 的评估, 完善 CTA/MRA 确认 LVO; 完善 CTP/MRI 检查计算梗死体积。

- 所有受试者或其合法代理人需签署知情同意书。

- 对纳入的受试者进行随机化。

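### Protocol V7.1 conflicts with itself on whether every patient has a baseline core volume, and the SAP has no rule for a patient without one

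*Supplement*

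**What the plan says.** Some parts of Protocol V7.1 call for a measured core in every patient:

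- Section 8.1 (Screening and Inclusion): "a CTP or MRI is required to calculate the infarct core volume". No exception is made for any ASPECTS range, and the Chinese text agrees: "完善 CTP/MRI 检查计算梗死体积".
- Section 8.6 (schedule): the row "Ischemic volume on CTP/DWI" is marked at baseline, with no footnote limiting it to a subset.
- Section 5.1: the real-time screening read covers core volume as well as ASPECTS and occlusion site.

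Other parts leave room for a patient without one:

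- Section 8.6, baseline imaging row: "CTA±CTP or MRI*+MRA±PWI". Footnote 1 adds: "For all enrolled cases, CT+CTA+CTP examination was the first choice before randomization".
- Section 1.2 joins ASPECTS and CTP/MRI with and/or as screening methods.
- Section 4.1.3 lists ASPECTS 3-5 as sufficient by itself. A core volume is named only for ASPECTS above 5 and below 3.

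Two planned analyses need the baseline value. Secondary endpoint 4 (section 7.2) is "Infarct core volume change from baseline", which under SAP 2.0, section 12, "will be analyzed using student t-test or Wilcoxon rank sum test as appropriate". The SAP also tests the interaction of treatment with core volume below 70 ml versus 70 ml or more.

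**The concern.** A site working from the schedule could take CT and CTA, agree an ASPECTS of 3-5 with the central readers, and randomise without CTP or MRI. Such a patient has no core by either definition in the protocol (rCBF below 30% on CTP, or ADC below 620 on MRI). The change score is then undefined and the patient belongs to neither subgroup level.

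At stake are one secondary endpoint and one of the ten subgroups. Patients without a baseline core would drop out silently, so the volume result would describe only those who had advanced imaging. The primary mRS analysis does not use core volume and is not affected.

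**Working it through.** The plan gives no figure to reproduce here, so the check is mainly a comparison of texts.

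**Step 1: is the measurement required?**

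| Place in V7.1 | What it implies |
|---|---|
| 8.1, English and Chinese | CTP or MRI required for all |
| 8.6, ischemic volume row | Volume expected at baseline for all |
| 5.1, screening read | Core volume is among the items read |
| 8.6, imaging row | CTP optional on the CT pathway |
| 8.6, footnote 1 | CT+CTA+CTP preferred, not mandatory |
| 1.2 | ASPECTS may be used with or without CTP/MRI |
| 4.1.3 | ASPECTS 3-5 qualifies with no volume named |

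The first three rows and the last four do not agree. Part of the conflict lies within one table: 8.6 expects the volume while marking its CT source as optional. The MRI alternative is not the problem. Its listed sequences include DWI and ADC, so MRI gives a core even without PWI. The gap is CT+CTA with neither CTP nor MRI.

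**Step 2: what happens to such a patient in the analysis?** Omitting the scan departs from 8.1 but breaks no inclusion criterion in 4.1.3. The full analysis set keeps all randomised subjects. SAP section 10 (Premature Withdrawal and Missing Data) leaves the primary endpoint unimputed in the main analysis, with LOCF and worst-case sensitivity analyses. For endpoints in general, it decides inclusion by whether post-baseline data exist. Neither rule covers a missing baseline value, and carrying values forward cannot create one.

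**Step 3: where can the loss fall?** The ASPECTS above 5 and below 3 routes both need a measured core of 70-100 ml. Only the ASPECTS 3-5 route can yield a patient without one. The overall share is

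f = (share of patients entering on ASPECTS 3-5) × (share of those with neither CTP nor MRI).

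The documents give neither factor. The scan precedes randomisation, so the loss should be similar in both arms.

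**Step 4: effect on precision, by assumption only.** With equal loss in the arms and an unchanged standard deviation, the standard error is multiplied by 1/√(1 − f). From 502/2 = 251 per arm:

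| Assumed f | Left per arm, 251(1 − f) | Standard error multiplier |
|---|---|---|
| 0 | 251 | 1.000 |
| 0.10 | 226 | 1.054 |
| 0.20 | 201 | 1.118 |
| 0.30 | 176 | 1.195 |
| 0.50 | 126 | 1.414 |

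The 251 already includes the 10% attrition allowance (452/2 = 226 per arm before it), so the counts are upper limits. The multipliers do not depend on the starting number. If 8.1 is followed, f is near zero and the first row applies. The higher rows show only how the cost would grow.

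**The case against.** A reader might infer that the plan by design lets ASPECTS 3-5 patients enter unmeasured, so that the endpoint cannot be scored for a large part of the trial. The documents do not support that. Section 8.1 requires the scan without exception, the schedule marks the volume for everyone, and SAP section 11 summarises core volume as a baseline characteristic. Section 1.5 says that with ASPECTS 3-5 "patients are enrolled without limitation of infarct core volume", but this lifts the 70-100 ml size limit and does not waive the measurement. Footnote 1 can fairly be read as ranking the CT package above the MRI package. The imaging workflow in Figure 2, which might settle the matter, is not shown. On this view a CT+CTA-only patient is a protocol deviation and there should be few of them.

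Most of that stands. It disposes of any claim of a built-in gap or of a known loss. Two things remain. The optional mark in 8.6 and the wording of 1.2 still contradict 8.1. And calling the patient a deviation does not remove them from the full analysis set or tell the analyst how to handle endpoint 4 and the subgroup.

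It can also be said that changing the analysis of endpoint 4 is more than this gap needs. That is fair as to the gap alone. The adjusted model is worth having on its own account, because the current comparison is unadjusted and baseline core and ASPECTS are natural covariates. Keeping patients without a baseline core is a further benefit.

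**Conclusion.** The point holds as a minor inconsistency. V7.1 gives conflicting instructions on whether a baseline core volume exists for every patient, and SAP 2.0 is silent on a patient without one. Any loss falls only on the ASPECTS 3-5 route. It affects the precision of secondary endpoint 4 and of the 70 ml interaction test, and the population they describe. It does not bias the comparison between arms, because the measurement precedes randomisation, and it does not touch the primary analysis.

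The size is unknown. It ranges upward from about zero if 8.1 is enforced, and the documents support no particular share.

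**What to change.** 1. **Protocol 8.6 and 1.2.** Align both with 8.1, so that the CT pathway does not show CTP as optional when no MRI is done. This adds no procedure, since 8.1 already states the requirement.

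2. **SAP section 12, infarct volume.** Replace the unadjusted t-test or Wilcoxon comparison of change with a model of follow-up volume, adjusted for baseline ASPECTS (recorded for all) and for baseline core. Use a missing indicator where the core was not measured; this is acceptable for a covariate fixed before randomisation. Keep the raw change as a supportive analysis in patients with both values. Name the follow-up scan as the protocol defines it (7-day or discharge NCCT, or 36-hour MRI), because the SAP currently specifies 36 hours by CT or MRI. The cost is that the headline becomes an adjusted difference, and that the wording of endpoint 4 in protocol 7.2 and of its test in 10.3.2 must be brought into line.

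3. **Subgroup table.** Show patients without a core value as a separate row beside the two 70 ml levels, so that the number left out of the interaction test is visible. This costs one line in the table.
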